# Effectiveness of a long-term use of a minimalist footwear versus habitual shoe on pain, function and mechanical loads in knee osteoarthritis: a randomized controlled trial

**DOI:** 10.1186/1471-2474-13-121

**Published:** 2012-07-12

**Keywords:** Osteoarthritis, Knee, Footwear, Shoe, Foot biomechanics, Gait

## Abstract

**Background:**

Recent studies have shown an important reduction of joint overload during locomotion in elderly women with knee osteoarthritis (OA) after short-term use of minimalist shoes. Our aim is to investigate the chronic effect of inexpensive and minimalist footwear on the clinical and functional aspects of OA and gait biomechanics of elderly women with knee OA.

**Methods/Design:**

Fifty-six elderly women with knee OA grade 2 or 3 (Kellgren and Lawrence) are randomized into blocks and allocated to either the intervention group, which will use flexible, non-heeled shoes— Moleca®—for six months for at least six hours daily, or the control group, which could not use these shoes. Neither group is undergoing physical therapy treatment throughout the intervention period. Moleca® is a women’s double canvas, flexible, flat walking shoe without heels, with a 5-mm anti-slip rubber sole and a 3-mm internal wedge of ethylene vinyl acetate. Both groups will be followed for six months and will be assessed at baseline condition, after three months, and after six months (end of intervention). All the assessments will be performed by a physiotherapist that is blind to the group allocation. The primary outcome is the pain Western Ontario and McMaster Universities Osteoarthritis (WOMAC) score. The secondary outcomes are global WOMAC score; joint stiffness and disability WOMAC scores; knee pain with a visual analogue scale; walking distance in the six-minute walk test; Lequesne score; amount and frequency (number of days) of paracetamol (500 mg) intake over six months; knee adduction moment during gait; global medical assessment score; and global patient auto-assessment score. At baseline, all patients receive a diary to record the hours of daily use of the footwear intervention; every two weeks, the same physiotherapist makes phone calls to all patients in order to verify adherence to treatment. The statistical analysis will be based on intention-to-treat analysis, as well as general linear models of analysis of variance for repeated measure to detect treatment–time interactions (α = 5%).

**Discussion:**

This is the first randomized, clinical trial protocol to assess the chronic effect of minimalist footwear on the clinical and functional aspects and gait biomechanics of elderly women with knee osteoarthritis. We expect that the use of Moleca® shoes for six months will provide pain relief, reduction of the knee adduction moment when walking, and improve joint function in elderly women with knee OA, and that the treatment, thus, can be considered another inexpensive and easy-to-use option for conservative OA treatment.

**Trial registration:**

NCT01342458

## Background

Osteoarthritis (OA) is the most common musculoskeletal disease [1,2], mainly affecting joints that suffer constant overload, such as the knee. As a consequence, routine daily activities, such as walking and ascending and descending stairs, as well as individual autonomy, may be compromised.

Knee adduction moment (KAM), usually used to estimate intra-articular overload, has been strongly related to OA severity [3] and its progression [4,5]—the higher the intra-articular load, the more severe will be the progression and functional consequences of the disease.

Great efforts have been made to improve conservative OA treatments, as, according to the Osteoarthritis Research Society International (OARSI) [6], the actual available pharmacotherapy is insufficient to control the clinical manifestations of OA. Surgical procedures have a high potential to reduce symptoms and improve function, but they are associated with increased costs, prolonged work impairment, and complications. According to the OARSI, conservative treatments, such as physical measures that allow improvement of biomechanical aspects and minimize intra-articular load, particularly KAM, produce the best evidence of efficacy. Braces for knee misalignments [7,8] and foot splints [9-13] are commonly used and frequently recommended as important interventions for the management of knee OA.

More recently, it has been suggested that foot flexibility during barefoot gait has the power to reduce the KAM in individuals with OA [14,15]. However, the opportunity to perform daily activities barefoot is rare and may be uncomfortable, especially for elderly people. There is scientific evidence that modern shoes, including the high-heeled, rigid-soled shoes commonly used by the majority of women in their everyday lives [16], generate higher knee moments and instability during locomotion. This is because modern shoes provide less flexibility, thereby not reproducing the degrees of freedom of the foot when it is bare, and causing progressive damage to knee joints with OA [17].

It has been shown that minimalist shoes that are capable of simulating barefoot gait reduced KAM in patients with knee OA [17-19]. More recently, we have shown that the acute use of an inexpensive, flexible, non-heeled footwear reduced significantly KAM in elderly women with OA during gait [20] and descending stairs [21].

Although it is reasonable to suppose a therapeutic effect of flexible, minimalist, and inexpensive shoes in the treatment of knee OA, its efficacy in reducing pain and KAM, as well as recovering musculoskeletal function in elderly people with knee OA has not been tested yet through a randomized, controlled trial. If effective, the use of these inexpensive, minimalist shoes might be part of a treatment prescription, representing a way of reducing costs associated with OA patients’ treatment.

Our hypothesis is that the use of the intervention footwear by elderly women with knee OA for at least six hours per day for six months could (i) relieve knee pain; (ii) improve musculoskeletal function in daily living activities; (iii) reduce knee load during gait; and (iv) reduce the use of medication, and, therefore, could be considered another inexpensive option for conservative OA treatment. Our aim is to investigate the therapeutic effect of inexpensive and minimalist footwear on the clinical and functional aspects of OA and gait biomechanics in elderly women with knee OA.

## Methods/Design

### Overview of the research design

A randomized, controlled trial was designed to study the effects of the shoe intervention on knee OA. Elderly women diagnosed with knee OA are recruited from hospitals and primary care centres, and are referred to a physical therapist, who performs the group allocation. The participants then are referred to another physical therapist, who performs the initial blind assessment.

All patients allocated to the intervention group (IG) receive the minimalist footwear on the first day and have to use it for six months, for at least six hours daily. The patients allocated to the control group (CG) do not receive the intervention footwear. All patients are assessed at baseline condition, after three months, and after six months (end of intervention). During this period, they continue to receive routine analgesic medication recommended by the medical staff at the hospital.

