**Figure 1 F1:**
[figure not shown]
Flowchart of the protocol steps.

After the recruitment, the patients are submitted to the inclusion and exclusion criteria by the physician (Process A). All patients are assessed in the biomechanics laboratory (Processes B and C) by a physiotherapist. This assessment represents the baseline condition. After three months, both groups are assessed according to Process B. At the end of the intervention period (after six months), both groups are assessed according to the complete protocol (Processes A, B, and C) (Figure 1).

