### Randomization and blinding

The randomization schedule was prepared using Clinstat software [26] by an independent researcher who was not aware of the numeric code for the control and intervention groups. A numeric block randomization sequence is kept in opaque envelopes.

After the patients’ agreement and assignment to participate in the research, the allocation into the groups is made by another independent researcher, who is also unaware of the codes. Only the physiotherapist responsible for the clinical trial knows who is receiving the intervention.

The initial and final clinical and medical examinations (Process A) are carried out by a rheumatologist who is blind to the patient’s allocation. One physical therapist (PT 2), who is blind to the treatment allocation, is responsible for all clinical, functional, and biomechanical assessments (Processes B and C). Another physical therapist (PT 1) is responsible for group allocation and monitoring the use of the intervention footwear by telephone. Both physiotherapists are blind to the block size used in the randomization procedure. The trial statistician is blind to treatment allocation until the main treatment analysis has been completed. To ensure that the researcher physiotherapists remain blind, they will emphasize to patients that they should not be told whether or not the patient has received the intervention footwear.

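### The only text that orders the two steps puts group allocation before the baseline assessment, so the self-reported baseline pain score, and with it the treatment-by-time test, can be influenced by knowledge of the arm

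*Protocol article*

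**What the plan says.** Under Overview of the research design, eligible women "are referred to a physical therapist, who performs the group allocation". The next sentence reads: "The participants then are referred to another physical therapist, who performs the initial blind assessment". The same section says that intervention patients "receive the minimalist footwear on the first day and have to use it for six months", without saying whether the shoes are handed over before or after the baseline questionnaires.

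Two other places touch on the sequence. The text under Figure 1 (Participants and recruitment) lists recruitment, the physician's eligibility check (Process A) and then the laboratory assessment (Processes B and C), adding "This assessment represents the baseline condition". It does not place allocation in that chain. Randomization and blinding puts allocation after the patient's agreement, but does not relate it to the baseline assessment.

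That section describes the allocator in two ways: "the allocation into the groups is made by another independent researcher, who is also unaware of the codes" and, in the next paragraph, "Another physical therapist (PT 1) is responsible for group allocation and monitoring the use of the intervention footwear by telephone".

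On blinding, it says "Only the physiotherapist responsible for the clinical trial knows who is receiving the intervention". It then describes the safeguard for the physiotherapists: patients are to be reminded that "they should not be told whether or not the patient has received the intervention footwear".

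Under Outcome measures, WOMAC pain is the primary outcome. Under Sample size and statistical analysis, outcomes are compared among baseline, three months and six months and between groups, by repeated-measures analysis of variance for the treatment-by-time interaction at 5%.

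**The concern.** A baseline is protected from the effects of allocation when it is recorded before anyone, the patient included, knows the arm. As written, the overview gives up that protection. Assessor blinding does not replace it, because WOMAC pain is the patient's own answer. The VAS, the Lequesne index and the global self-assessment are self-reported too. Asking patients not to reveal whether they have the shoes presupposes that they know.

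The stakes are higher here because baseline enters the primary test as an outcome level. A between-arm difference in baseline reporting that is absent later goes in full into the difference in change. Adjusting for baseline would reduce the problem without removing it.

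The two descriptions of the allocator add to the uncertainty, since they leave open who opens the envelope and when the arm becomes known.

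**Working it through.** **Step 1: the order.** The relevant texts, side by side:

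| Protocol section | Places allocation relative to baseline? |
|---|---|
| Overview of the research design | Yes: allocation first, then the initial assessment |
| Text under Figure 1 | No: Process A, then B and C, with allocation not mentioned |
| Randomization and blinding | No: after consent only. It does call the initial examination blind to allocation, which fits allocation having taken place already |

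One text gives an order and none reverses it. Figure 1 itself is not shown in the text at hand.

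**Step 2: what a baseline-only shift would do.** The protocol gives no figure on this point, so there is none to reproduce. Inputs from the protocol: 28 per arm (N = 56), three visits, α = 0.05. Assumptions: a between-arm shift b at baseline only (in SD units), no true effect, equal variances, and a correlation r between visits. The protocol states neither b nor r.

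*Two-visit comparison (baseline to six months).* SE of the difference in change = √(2/28) × √(2(1 − r)).

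- r = 0.5: SE = 0.267. For b = 0.2 the z-shift is 0.2/0.267 = 0.75, and P(|Z| > 1.96) = 11.6%.
- r = 0.7: SE = 0.207. For b = 0.2 the z-shift is 0.97, and the probability is 16.2%.
- b = 0.1 at r = 0.5: 6.6%.

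*Planned three-visit interaction test.* A shift b in one arm at baseline gives interaction deviations of ±b × (1/3, −1/6, −1/6). The sum of squares is N × b² × (1/9 + 1/36 + 1/36) = N b²/6. The noncentrality is therefore λ = N b² / (6(1 − r)), with 2 and 108 degrees of freedom.

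| b | r | λ | Two-sided error |
|---|---|---|---|
| 0.2 | 0.3 | 56 × 0.04/4.2 = 0.53 | 9.1% |
| 0.2 | 0.5 | 56 × 0.04/3.0 = 0.75 | 10.9% |
| 0.2 | 0.7 | 56 × 0.04/1.8 = 1.24 | 15.2% |
| 0.1 | 0.5 | 56 × 0.01/3.0 = 0.19 | 6.4% |

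Simulation with 20,000 runs per setting gave 8.9%, 10.5% and 15.0% for b = 0.2 at r = 0.3, 0.5 and 0.7. With b = 0, which taking baseline before disclosure secures by design, it gave 4.9% to 5.0%.

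**Step 3: direction.** Suppose that expectation lowers reported baseline pain in the shoe arm, or disappointment raises it in controls. The shoe arm's improvement then looks smaller than it is. In the two-visit case with b = 0.2 and r = 0.5, the 11.6% splits into about 11.3% in favour of control and 0.3% in favour of the shoe. At r = 0.7 the split is about 16.0% and 0.2%. A shift the other way gives the mirror image.

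**Step 4: a stable shift.** If knowledge of the arm moves reporting by the same b at all three visits, the between-arm differences are (b, b, b). All interaction deviations are then zero and the test is unaffected.

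**Step 5: baseline adjustment.** An analysis of covariance subtracts r times the baseline difference, so a baseline-only shift leaves a bias of r × b. For b = 0.2 this is 0.10 SD at r = 0.5 and 0.14 SD at r = 0.7, against 0.20 SD for the difference in change.

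**The case against.** The strongest reply is that the protocol never says when a patient learns her arm. Allocation uses a numeric code in opaque envelopes, one description has the allocator unaware of the codes, and only the responsible physiotherapist is said to know who receives the intervention. Allocation could be recorded before it is disclosed, and the shoes could be handed over later the same day. The overview is a summary, and the flowchart may show a clearer order. This stands: a reader might infer that patients certainly know their arm at baseline and that the result is biased, but the documents support only that they may know and that the result can be biased.

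The size is also open to challenge. The inflation requires a shift at baseline that is missing later, yet patients know their arm at three and six months as well. The mechanisms that come first to mind would also work against the shoe, so a false claim of benefit would become less likely. Both points are right and limit the illustration. A bias against the shoe is still a bias, however, and could hide a real effect.

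Three stronger readings are tempting and should not be made:

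- **Baseline knee adduction moment carries a shoe effect.** The Background reports reductions with acute use. Nothing says that the effect persists after the shoe is removed, or that baseline gait is recorded in the shoes or after wearing them.
- **Patients could be found ineligible after allocation.** Eligibility is settled in Process A by the rheumatologist. The physical therapist's assessment comprises Processes B and C, which are not screening.
- **Concealment has failed because PT 1 allocates.** The same section provides opaque envelopes, block randomization and physiotherapists blind to block size. The two descriptions may be two steps of one procedure. They need reconciling but do not prove a failure.

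The 72-hour recall of WOMAC also limits any true effect of shoes received that day on the period rated. It does not protect the answers from the patient's knowledge of her arm.

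**Conclusion.** The point holds as a risk that the text creates and leaves unresolved. The only stated order is allocation first. The primary outcome is self-reported, only assessors are shielded, and baseline is part of the tested interaction. Following the protocol as written exposes the primary analysis to an avoidable bias.

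The size cannot be derived from the documents. For a 0.2 SD shift confined to baseline, the error is about 11–16% at correlations of 0.5 to 0.7; for 0.1 SD at a correlation of 0.5 it is about 6–7%. The direction is uncertain and the bias disappears if the shift is the same at every visit. Whether patients in fact know their arm at baseline is a likely inference, not a statement in the protocol.

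**What to change.** Revise the overview, and Figure 1 if it shows the same order, to state one sequence: consent, Process A, baseline Processes B and C, baseline record locked, and only then envelope opened, arm disclosed and shoes issued.

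Reconcile who allocates in the overview and in Randomization and blinding. The independent researcher already named there is preferable to PT 1, who also monitors shoe use.

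Recruitment has been open since March 2011. For patients already enrolled, record whether baseline came before or after the arm was disclosed, and run a sensitivity analysis by that order.

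The cost is small: the same visits and staff, a revised paragraph, possibly the flowchart, and one recorded item for patients already enrolled. If practice already follows this sequence, only the wording needs correcting.

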### Participants and recruitment

This study is currently recruiting patients (study start date: March 2011).

The eligibility criteria are:

Women 60 to 80 years of age

OA diagnosed according the American College of Rheumatology - ACR [22] criteria

Radiographic evidence of medial femorotibial classified as Kellgren–Lawrence [23] grade 2 or 3

Absence of diagnosed hip and/or ankle OA, rheumatoid arthritis, or systemic inflammatory arthritis; asymptomatic OA of both knees

Knee pain between 3 and 8 on a VAS

Body mass index (BMI) <35 kg/m^2^[17]

No history of surgical procedure on knee, ankle, or hip, and no muscle injury in the last six months

Absence of diagnosed neurological disease [24]

Leg length discrepancy smaller than 1 cm

Absence of rigid hallux [12]

Absence of arthroplasty and/or lower limb orthoses or indication of lower limb arthroplasty throughout the intervention period

Currently not using the Moleca® or similar shoes for more than 25 hours per week

No knee intra-articular steroid or hyaluronic acid three and six months, respectively, before inclusion in the study [12]

Absence of knee instability (verified by clinical examination to assess the collateral and cruciate ligaments)

Absence of dementia or inability to give consistent information [24]

Ability to walk independently without an assistive device for at least six hours a day

No physical therapy or acupuncture treatment throughout the intervention period

The use of paracetamol 500 mg every four hours is permitted for both groups for the control of pain, according to ACR recommendations for OA treatment [25]. NSAIDs and DMARDs are allowed if initiated at least eight and four weeks, respectively, prior to randomization, and they must be used in stable doses throughout the study [12].

The participants are recruited from three settings: (a) rheumatology clinic medical care located at the Hospital das Clínicas of the School of Medicine at the University of São Paulo, (b) orthopaedic ambulatory medical care located in the University Hospital, and (c) a primary care centre at the School of Medicine of the University. All potential patients are interviewed by telephone and, when selected, are assessed, in the rheumatology clinic of the Hospital das Clínicas of the School of Medicine at the University of São Paulo, by a rheumatologist who is blind to the patient’s allocation (Process A). The design and flowchart of the steps of the protocol are presented in Figure 1.

**Figure 1 F1:**
[figure not shown]
Flowchart of the protocol steps.

After the recruitment, the patients are submitted to the inclusion and exclusion criteria by the physician (Process A). All patients are assessed in the biomechanics laboratory (Processes B and C) by a physiotherapist. This assessment represents the baseline condition. After three months, both groups are assessed according to Process B. At the end of the intervention period (after six months), both groups are assessed according to the complete protocol (Processes A, B, and C) (Figure 1).

### Randomization and blinding

The randomization schedule was prepared using Clinstat software [26] by an independent researcher who was not aware of the numeric code for the control and intervention groups. A numeric block randomization sequence is kept in opaque envelopes.

After the patients’ agreement and assignment to participate in the research, the allocation into the groups is made by another independent researcher, who is also unaware of the codes. Only the physiotherapist responsible for the clinical trial knows who is receiving the intervention.

The initial and final clinical and medical examinations (Process A) are carried out by a rheumatologist who is blind to the patient’s allocation. One physical therapist (PT 2), who is blind to the treatment allocation, is responsible for all clinical, functional, and biomechanical assessments (Processes B and C). Another physical therapist (PT 1) is responsible for group allocation and monitoring the use of the intervention footwear by telephone. Both physiotherapists are blind to the block size used in the randomization procedure. The trial statistician is blind to treatment allocation until the main treatment analysis has been completed. To ensure that the researcher physiotherapists remain blind, they will emphasize to patients that they should not be told whether or not the patient has received the intervention footwear.

### Protocol assessments

Eligible patients are assessed according to Process A, which consists of an interview and a clinical examination to classify the patient’s overall health condition, performed by the rheumatologist (global medical assessment score 1–5) and by the patient (global patient self-assessment score). Full-extension anterior–posterior knee radiographs are used to confirm the OA diagnosis and classification according to Kellgren–Lawrence criteria [23]. Process A is performed by a rheumatologist who is blind to the patient’s allocation. The two overall health condition assessments are conducted at baseline and at the end of the intervention period by the same physician.

At baseline, patients from both groups receive a diary to record the amount, in hours, of Moleca® use, and the intake of paracetamol tablets (500 mg) on a daily basis. Every three months, the diaries are collected in order to account for the Moleca® and painkillers use (Table 1).

**Table 1 T1:** Diary of intervention shoe use and Paracetamol intake

**NAME:____________________________________________________________________MONTH ** – First day:_____/_____/_____Final day: _____/_____/_____															
**DATE**	/	/	/	/	/	/	/	/	/	/	/	/	/	/	/
